**Staff**									
	Staff impact (engagement)	1		Quantitative		CHOICE web app data from clinician dashboard: number and type of log-ins		All data	
	Staff impact	1		Quantitative		NHS Friends and Family Test		Minimum of twice: baseline (on registration) and after using CHOICE for several months	
	Staff behavior	1		Quantitative		NoMAD^g^ questionnaire		At interview or by email and by email request toward the end of the evaluation	
	Staff impact	1 and 9		Qualitative		Focus groups (staff)		Once: planned but unable to happen because of the COVID-19 pandemic	
	Staff impact	1 and 9		Qualitative		One-on-one interviews (staff)		Once for key staff who are not available for the on-site focus group; toward the end of the project	
	Staff experience	7		Quantitative		R-Outcomes surveys		Baseline (on registration) and every 6 months	
**Services**									
	Spread, equity of access, and resource use	3, 4, and 8		Quantitative		Clinic activity information		See Multimedia Appendix 1 for more details	

^a^CHOICE: cochlear implant home care.

^b^NHS: National Health Service.

^c^PAM: Patient Activation Measure.

^d^CI-EMP: Cochlear Implant Empowerment Scale.

^e^EQ-5D-5L: EuroQol 5-Dimension 5-Level.

^f^HUI3: Health Utilities Index Mark 3.

^g^NoMAD: Normalization Measure Development.

#### Primary Research Questions

This study attempts to answer the following primary research questions:

Evaluation: What is the impact of the rollout of the new care pathway on users of the program (people with cochlear implants and the staff)?Research: Does the new care pathway increase empowerment for people with cochlear implants while having no detrimental effect on their hearing and quality of life?

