#### Proposed Sample Size

We do not yet know what proportion of patients will choose to follow this pathway, as the previous study was a single-center randomized controlled trial involving a limited number of patients [10]. However, 7 centers care for approximately one-third of the approximately 12,000 adults [28] with cochlear implants in the United Kingdom. At the early stages of project planning, we estimated that if 40% of patients enrolled, this may involve approximately 1700 patients. We expect this to be the upper limit for recruitment. Scaling up a digital health tool for people with cochlear implants has not been done before; thus, we cannot predict the uptake. We anticipate that up to 10 members of staff per will be involved per site (total 70). As the aim of the project was not to formally test a hypothesis, a sample size calculation was not conducted.

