#### Quantitative

Descriptive statistics and graphs will be used to present the data. Data will be displayed visually wherever possible to facilitate sharing with various stakeholders. The significance value will be set at *P*=.05, including Bonferroni corrections for multiple comparisons where appropriate. All repeated-measures data will be compared at baseline and follow-up using analysis of variance to examine any changes in empowerment, hearing, and quality of life in the participants. Surveys will be analyzed at the baseline and follow-up time points using inferential statistical analyses. The choices of participants in the DCE will be subjected to conditional logit model analysis using the *survival* package of the R programming language.

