The PAM may not be very sensitive to changes in the empowerment of people using cochlear implants because of its medical perspective. Given that this is the first time there has been a large-scale rollout of a remote care model for cochlear implants, we do not know how many people will participate. Low patient numbers and dropouts are likely to affect the quality of the results, although reporting them will provide important information on the success of the implementation. Patients who discontinue the use of CHOICE will be asked to provide a reason for their withdrawal.

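### Primary question 2 asks for no detriment to hearing and quality of life, but the only stated inferential method is a test of change, which cannot show absence of detriment

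*Protocol article*

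**What the plan says.** Under Primary Research Questions, the research question has two halves: empowerment should increase, "while having no detrimental effect on their hearing and quality of life".

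Under Data Analysis, Quantitative, one method serves both halves: "All repeated-measures data will be compared at baseline and follow-up using analysis of variance to examine any changes in empowerment, hearing, and quality of life". The same paragraph adds "The significance value will be set at *P*=.05", "including Bonferroni corrections for multiple comparisons where appropriate". Descriptive statistics and graphs are also planned.

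Under Proposed Sample Size the article states: "As the aim of the project was not to formally test a hypothesis, a sample size calculation was not conducted". On numbers it says "we estimated that if 40% of patients enrolled, this may involve approximately 1700 patients", calls this the expected upper limit, and adds that uptake cannot be predicted. The Limitations section warns: "Low patient numbers and dropouts are likely to affect the quality of the results".

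Under Patient Outcomes, Quantitative Measures, global rating of change scales are to show whether changes observed in PAM, CI-EMP, HUI3 or EQ-5D-5L were perceived by patients. The home hearing check is not in that list.

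**The concern.** The two halves of the question need different evidence. A test of the hypothesis of no change can support a claim that empowerment rose. It cannot support a claim that hearing and quality of life did not fall, because a non-significant result arises both when nothing changed and when too few pairs were available to see the change.

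Bonferroni works in opposite directions on the two halves. For empowerment it guards against a false claim of benefit. Applied to hearing or quality of life, it raises the bar for detecting harm.

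At stake is half of a primary conclusion. The Participants section says that CHOICE may be offered to all sites depending on the evaluation. If the achieved number of pairs is small, imprecision could be taken for stability.

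**Working it through.** **Plan's own figure.** The article gives no power, margin, effect size or SD for these outcomes, so there is no such calculation to reproduce. The 1700 is an enrolment estimate and not a count of complete pairs.

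**Inputs from the article.** Test of change between baseline and follow-up; significance level .05; Bonferroni where appropriate, number of comparisons not given; upper limit of about 1700 patients.

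**Assumed inputs.** True mean worsening d of 0.1, 0.2 or 0.3 in units of the SD of change; number of complete pairs n from 50 to 1700; Bonferroni divisor k of 1 (none) or 3 (one each for the home hearing check, HUI3 and EQ-5D-5L). A two-timepoint repeated-measures analysis of variance is equivalent to a two-sided paired test.

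**Chance that a true worsening is non-significant** (normal approximation):

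P(miss) = 1 − Φ(d√n − z), with z = 1.960 for k = 1 and z = 2.394 for k = 3 (two-sided .05/3).

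Worked case, d = 0.2, n = 100, so d√n = 0.2 × 10 = 2.0:
- k = 1: 1 − Φ(0.040) = 48%
- k = 3: 1 − Φ(−0.394) = 65%

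The noncentral t gives 49% and 66%, so the approximation is adequate.

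| Complete pairs | d = 0.1, k = 1 / 3 | d = 0.2, k = 1 / 3 | d = 0.3, k = 1 / 3 |
|---|---|---|---|
| 50 | 89% / 95% | 71% / 84% | 44% / 61% |
| 100 | 83% / 92% | 48% / 65% | 15% / 27% |
| 200 | 71% / 84% | 19% / 33% | 1% / 3% |
| 400 | 48% / 65% | 2% / 5% | <1% / <1% |
| 1700 | 2% / 4% | <1% / <1% | <1% / <1% |

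Down each column the size of the decline is fixed and only the number of pairs changes. For d = 0.2 without correction, the chance of a non-significant result runs from 71% at 50 pairs to practically nil at 1700.

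**The alternative rule.** Suppose a decline of size m (in SD of change) is called excluded only when the two-sided 95% confidence interval lies wholly on the better side of m. If the true decline equals m, the chance of wrongly excluding it on one outcome is 2.5% at any n. Pairs needed per outcome when the true change is zero:

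n = ((1.960 + z_power)/m)², with z_power = 0.842 (80%) or 1.282 (90%).

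- m = 0.1: 785 / 1051
- m = 0.2: 197 / 263
- m = 0.3: 88 / 117

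These margins are illustrations, since the article states none. The chance that all three outcomes pass together is lower than the per-outcome power. For precision, the interval half-width is 1.96/√n: 0.28 SD at 50 pairs, 0.20 at 100 and 0.10 at 400.

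**Does another stated element fill the gap?**
- The global rating of change qualifies changes that have been observed. It says nothing about a decline that the test did not detect, and it does not list the home hearing check.
- The home hearing check's comparison with baseline, and the resulting flag, are a screen for the individual patient. They are not a rule for the study's conclusion.
- Adverse events and missed issues are collected, but no group-level criterion for hearing or quality of life is attached to them.

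**The case against.** The strongest reply is that the article never says a non-significant result will be read as no detriment. It says only that changes will be examined, alongside descriptive statistics and graphs. That stands: a reader might infer a fixed pass rule, but no sentence contains one. A margin might also sit in an analysis plan that is not shown. The point therefore rests on the method that is stated, a test of change for a no-harm question, and not on a missing detail.

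Four further limits also stand.
- Bonferroni is conditional and nothing says that it will be applied to hearing or quality of life. The uncorrected miss rates make the point without it.
- A reader might infer that with high uptake a trivial decline would be reported as harm. For quality of life the global rating of change partly answers that, so the stronger reading is not supported.
- It would be too categorical to say that a real loss of hearing would go unreported, because individual hearing flags, adverse events and missed issues are also collected.
- The article explains openly why no sample size was calculated, and data collection is complete. Criticism of the sample size can change nothing now.

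The reply that no hypothesis is formally tested does not remove the problem. The analysis section sets a significance level for outcomes that belong to a yes/no primary question.

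**Conclusion.** The concern holds in this limited form: the stated test does not match the no-harm half of primary question 2, and non-significance from it should not be taken as absence of detriment. With 100 complete pairs a true 0.2 SD worsening would be non-significant about half the time uncorrected (48%) and about two-thirds of the time with a divisor of 3 (65%). At 1700 pairs it would almost never be missed. How much this matters depends on the number of complete pairs, which the article does not give. The effect sizes and the divisor are assumptions, but more pairs always lower the miss rate and a correction always raises it.

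A margin rule cures only the confusion of imprecision with stability. There is no control group on the same measures, the article names the pandemic as the likely largest confounder, and it expects data mostly missing not at random, with those who find CHOICE less helpful dropping out. The result can therefore describe within-patient change among completers, and not the causal effect of the pathway.

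**What to change.** The Results section reports that, as of July 2021, the research data had not been analysed. If that is still so, make these changes before analysis:

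1. State a largest tolerable mean decline for each of the home hearing check, HUI3 and EQ-5D-5L, with a reason for each.
2. Report the mean change and its 95% confidence interval on each. Do not apply Bonferroni here, because all three must pass and requiring all to pass does not inflate the chance of a false no-harm statement.
3. Say that a decline of the stated size is excluded only if every interval excludes it. Otherwise report that detriment is not excluded.
4. Word the conclusion as within-patient change among those with both measurements, and give the no-control, pandemic and missing-data caveats beside it.
5. Reconcile the statement under Proposed Sample Size that no hypothesis is formally tested with the significance testing under Data Analysis.

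If the data have already been analysed, report the intervals and do not claim no detriment from non-significant tests.

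The cost is wording in the analysis plan and agreement on three tolerable declines; no new data are needed. The downside is that with few pairs the conclusion may have to be that detriment is not excluded.

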#### Secondary Research Questions

This study attempts to answer the secondary research questions provided in Textbox 1.

Secondary research questions.3. What is the extent of the spread of the new care pathway?What has facilitated the adoption of the new care pathway?What has hindered the adoption of the new care pathway?4. Does the new care model improve patients’ confidence to self-manage their cochlear implant as measured by patient-reported outcomes of health confidence, health status, and personal well-being?Do patients initiate review appointments with the service rather than rely on or wait for appointments scheduled by the service?5. Does the new care model improve patients’ experience of follow-up care?Do patients engage with the technology as measured by patient-reported outcomes of digital confidence and perceived value of the tool?6. Does the new care model improve equity of access to follow-up care?7. Does the new model of care improve the experience of staff working in the service, as measured by staff-reported outcomes of job confidence and work well-being?Do staff have confidence in the new care model, as measured by staff-reported outcomes of digital confidence and perceived value of the tool?Do they recommend it?8. Does the new care model improve the use of resources by reducing the need for follow-up appointments and enabling the service to be delivered by a different skill mix?9. What lessons can be learned from the implementation process that will benefit the spread and adoption of this model?

#### Patient Outcomes

##### Quantitative Measures

All data will be downloaded from the CHOICE web app, and patient use of all elements of CHOICE, including the hearing check, will be assessed. Errors in CHOICE, adverse events, and missed patient issues will be collected during the study period. Patients who take part in the focus group or interview will be asked to complete a short survey about the cost implications of switching to remote care (eg, impact on travel costs and need for childcare).

Quantitative data about patients’ use of CHOICE will be collected using the R-Outcomes survey tool [30]. These measures share a common framework with 4 items and 4 responses suitable for use on a mobile device and are validated, short, and have a lower reading age than other measures. R-Outcomes are incorporated into CHOICE and will assess the patients’ health, well-being, health confidence, digital readiness, and user experience. The NHS Friends and Family Test was also incorporated into the CHOICE web app, asking the question, “How likely are you to recommend this service to friends and family if they need similar care or treatment?” with 6 response options ranging from *extremely likely* to *extremely unlikely* [31].

We will use the following measures to assess empowerment, health-related quality of life, hearing, and patient care pathway preference: Patient Activation Measure (PAM), Cochlear Implant Empowerment Scale (CI-EMP), EuroQoL 5-Dimension 5-Level (EQ-5D-5L) questionnaire, Health Utilities Index Mark 3 (HUI3), a global change rating, and a discrete choice experiment (DCE). PAM is a well-validated generic measure of patient activation that evaluates the knowledge, skills, beliefs, and behaviors that patients have for self-management of their long-term condition [32,33]. The CI-EMP is a questionnaire specifically designed to measure how empowered people are to manage their own cochlear implant care [34]. The EQ-5D-5L is a standardized health outcome measure comprising five dimensions: mobility, self-care, usual activities, pain or discomfort, and anxiety or depression [35]. The HUI3 is a multi-attribute health status classification system that evaluates eight domains: vision, hearing, speech, ambulation, dexterity, emotion, cognition, and pain [36].

The global rating of change scales will be used to capture whether patients perceive a change in their hearing, empowerment, and quality of life to determine whether any changes observed in the PAM, CI-EMP, HUI3, or EQ-5D-5L are meaningful; that is, whether they were perceived by patients.

We designed a DCE to assess the effects of the following five care pathway attributes on the preferences of the participants for remote care (Figure 2):

Who decides when the next clinic appointment will be?When is the ability to understand speech monitored?Who can fine-tune the cochlear implant?Where can patients get rehabilitation and troubleshooting information that is personalized to their needs?How are upgrades to sound processors provided?

**Figure 2 figure2:**
[figure not shown]
The 5 elements of the discrete choice experiment.

Each attribute had 3 levels that described different approaches and degrees of remote care; for example, the choices for who decides when the next clinic appointment will be *the implant clinic*, *the patient,* or *the implant clinic (however, the patient can request appointments when required)*. The experiment was constructed using the mix and match design method [37], as implemented in the *support.CEs* package for the R statistical environment [38]. The experimental design was organized into 2 blocks to reduce the number of questions each participant had to complete, and patients will be randomly assigned to complete either block 1 or block 2. The design requirements of 5 attributes per alternative, 2 alternatives per choice question, and 2 experimental blocks resulted in the allocation of 9 discrete choices per block. The role of the DCE is to help us learn about how the different elements of the care pathway interact to shape participant preferences for remote care compared with the usual pathway. It is possible that the preferences that patients have for remote care could relate to their outcomes, and we will explore these relationships using exploratory correlational analyses.

##### Qualitative Measures

Although the qualitative fieldwork was initially planned as focus groups of patients and staff at each site, because of the COVID-19 pandemic, this changed to telephone or web-based interviews. Up to 20 patients per site will be recruited. The interviews will be audio recorded, transcribed, and managed using NVivo (version 12; QSR International); 2 Wessex AHSN qualitative evaluators will conduct all interviews.

#### Staff Outcomes

##### Quantitative Measures

CHOICE web app data about staff use of the clinician dashboard will be downloaded and analyzed. The staff will also be asked to complete the NHS Friends and Family Test and R-Outcomes (with additional measures of work well-being and innovation adoption) within the CHOICE clinician dashboard.

##### Qualitative Measures

As for patients, focus groups were planned but changed to telephone or web-based interviews because of the COVID-19 pandemic; up to 10 staff per site will be recruited for one-on-one interviews.

##### Services Outcomes: Quantitative Measures

Local service-level activity data will be collected at all sites with a view to assessing resource use and the workforce (Multimedia Appendix 1). We aim to obtain data from all clinic patients to maximize the sample size. A cohort of patients will also be identified for comparison. This will comprise patients registered with clinics but who have not yet been offered the new care model. We will look at the aggregated clinical activity before and after the introduction of the tool (eg, numbers of outpatient appointments and DNAs in the inclusion group). There will not be a control group of patients undergoing the same measures as the intervention group. We will also analyze the centers’ previously collected service-level data to evaluate the current pathway.

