## Discussion

### Limitations

A total of 7 sites agreed to participate in the implementation and evaluation of CHOICE. These sites are mostly larger adult cochlear implant centers in England. Sites were self-selected: those participating were the centers that expressed interest in taking part. This means that it is unlikely that these centers are representative of all UK adult cochlear implant centers; they are likely to be more willing to innovate. Given that data collection will commence as soon as centers and patients join CHOICE, there will be variable periods of follow-up.

We expect significant effect modification in subgroups (eg, by age, gender, cochlear implant center, and other demographic factors). Assessing and reporting effect modifications may help identify a subset of patients who would not benefit from remote care. We attempted to control for confounding factors by collecting the demographic and digital readiness data. However, it is possible that there are confounders that remain unaccounted for; for example, we will not collect data on mental health and social support or the impact of the COVID-19 pandemic. It is likely that the concurrent COVID-19 pandemic will be the largest confounding factor in the data. In addition, the coincidental launch of a manufacturer-led remote care pathway (Cochlear Remote Check) for patients with some devices is likely to confound the results. The nature of recruitment for this study (cochlear implant center choosing to be involved and patient choosing to take part) means that there is likely to be a significant bias. Patients who choose to take part in a trial of remote care may not be representative of the broader population of people with cochlear implants. As recruitment is performed via patient and clinic choice, it is not valid to have a control group of people who do not follow a remote care pathway.

We are aiming for 6 months of follow-up data. This may be insufficient to highlight the benefits and limitations of remote care, especially in the climate of change because of the COVID-19 pandemic. In addition, as patients are encouraged to register for CHOICE at any point, there may only be a very short experience of using CHOICE by the end of data collection for many people.

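### The only service-activity contrast described is before versus after CHOICE, which cannot separate its effect on appointments from the pandemic's, and no described analysis uses the planned not-yet-offered cohort

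*Protocol article*

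**What the plan says.** All of the following is in the protocol article.

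- **Contrast.** Under Services Outcomes: Quantitative Measures: "We will look at the aggregated clinical activity before and after the introduction of the tool". The example in brackets is "numbers of outpatient appointments and DNAs in the inclusion group".
- **Data scope.** Same section: "We aim to obtain data from all clinic patients to maximize the sample size".
- **Comparison cohort.** Same section: "A cohort of patients will also be identified for comparison". It is defined in the next sentence: "This will comprise patients registered with clinics but who have not yet been offered the new care model".
- **Controls.** Same section: "There will not be a control group of patients undergoing the same measures as the intervention group". Limitations goes further. Because patients and clinics choose to take part, "it is not valid to have a control group of people who do not follow a remote care pathway".
- **Pandemic.** Limitations: "It is likely that the concurrent COVID-19 pandemic will be the largest confounding factor in the data". The same paragraph says that data on the pandemic's impact will not be collected.
- **Use of the result.** Question 8 (Secondary Research Questions) asks whether the model improves resource use through less need for follow-up appointments. Assessment of Resource Use and Workforce adds an economic analysis of clinic activity and predictive modeling of further scale-up.
- **Methods.** The Quantitative part of Data Analysis gives analysis of variance for repeated measures, unspecified inferential analyses for surveys, and a conditional logit model for the choice experiment. It names no method for the activity data or for the comparison cohort.

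**The concern.** Question 8 is causal: does the new pathway reduce the need for appointments? A before-after contrast answers it only if activity would otherwise have stayed level. The protocol itself gives reason to doubt that, since data collection ran from June 2019 to January 2021 and the pandemic is expected to dominate the confounding. If clinic attendance fell for reasons unrelated to CHOICE, the contrast would show a reduction that favors the intervention, and that reduction could pass into the economic analysis and the scale-up modeling.

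The plan already contains a group that could show what happened without the tool: patients at the same clinics, in the same months, who had not been offered it. The text does not connect this group to the analysis, and one sentence can be read as ruling it out. Two analysts following the article could reach opposite decisions about using it.

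**Working it through.** The article gives no appointment rate, DNA rate, power or expected change for the service outcome, so there is no stated figure to reproduce. The check has four parts.

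**1. What the contrast estimates.** Let t be the true proportional reduction in appointments due to CHOICE, d the proportional fall due to outside causes, and w the share of the after period affected. All three are unknown. Then

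- before-after ratio = (1 − t)(1 − d·w)
- ratio for a comparator with the same outside trend = 1 − d·w
- controlled ratio = (1 − t)(1 − d·w) / (1 − d·w) = 1 − t

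One observed before-after ratio cannot determine t. A ratio of 0.70 arises from t = 0, d = 0.30, w = 1, and equally from t = 0.30, d = 0. With assumed inputs:

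| t | w | d = 0.10 | d = 0.30 | d = 0.50 | Controlled ratio |
|---|---|---|---|---|---|
| 0 | 1 | 0.90 | 0.70 | 0.50 | 1.00 |
| 0 | 0.5 | 0.95 | 0.85 | 0.75 | 1.00 |
| 0.20 | 1 | 0.72 | 0.56 | 0.40 | 0.80 |
| 0.20 | 0.5 | 0.76 | 0.68 | 0.60 | 0.80 |

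The table shows how the bias works, not how large it is in this project. The last column holds only if both groups share the same outside trend.

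**2. How much of the window could be affected.** Project Design and Setting gives June 11, 2019 to January 31, 2021, which is 601 days counted inclusively. No pandemic onset date is stated. For assumed dates:

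- February 1, 2020: 366/601 = 60.9%
- March 16, 2020: 322/601 = 53.6%
- April 1, 2020: 306/601 = 50.9%

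These are shares of the project-wide window. Each clinic starts once its own approvals are in place, and the start dates are not given. The share of any one site's after period is therefore unknown, and for a late starter it could be all of it.

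**3. Counts against rates.** If B appointments are booked and a constant proportion p is not attended, the DNA count is p·B. If bookings fall by a fraction d, the count becomes p·B·(1 − d), a fall of d with no change in attendance behavior. Project Design and Setting also expects follow-up length to differ by clinic, so raw counts need person-time or booking denominators even without a pandemic.

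**4. The two statements on controls, side by side.** Services Outcomes plans a comparison cohort and then says that no control group will undergo the same measures as the intervention group. Limitations says that a control group not following remote care is not valid, because taking part is a choice. Taken literally, that second statement includes patients not yet offered CHOICE. Its reason, self-selection by patients, does not apply to them in the same way, since they have neither accepted nor declined. The statements can be made consistent if the Limitations sentence is meant for patient-completed measures only, but the article does not say so.

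**The case against.** The strongest reply is that the article leaves detail out rather than making an error. The cohort is labeled as being for comparison, so it has a purpose. How it enters a model could be set out in Multimedia Appendix 1 or a fuller plan, neither of which is shown. The inclusion group appears only in an example, and data are sought from all clinic patients. The pandemic is openly disclosed, question 8 is secondary, no formal hypothesis test is claimed, and findings are to be triangulated with qualitative work.

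Much of this stands, and it rules out stronger readings that a reader might infer:

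- **That the cohort has no role.** It has a stated purpose. What is absent is any described analysis that uses it.
- **That the protocol declares this cohort invalid.** Limitations does not name it, and its reason is self-selection.
- **That activity will be analyzed only in enrolled patients.** The example does not establish this.
- **That the bias is some particular percentage.** Onset date and size of the external fall are both assumptions.
- **That the evaluation will credit CHOICE with the pandemic's effect.** The stated limitations suggest caution in interpretation.

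The reply does not remove the core. The before-after contrast is a choice the article states, not a gap. Disclosing a confounder does not take it out of the estimate, and Limitations offers no remedy for activity data. The appendix is described as a specification of activity information and its sources, not as an analysis.

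The reply also limits the remedy. Comparing enrolled with not-yet-offered patients would drop those who were offered CHOICE and declined, bringing in the self-selection that the protocol warns about. Similar trends before CHOICE cannot prove that both groups would respond alike to the pandemic.

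**Conclusion.** The point holds in this form: the one service-activity contrast described cannot attribute a fall in appointments to CHOICE, on the protocol's own account of the pandemic. The comparison cohort that could reduce the problem is planned but not tied to any described analysis, and the wording in Limitations literally excludes it.

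The bias would favor CHOICE if outside causes reduced attendance, and its size cannot be computed from the documents. The ratios and window shares above rest on assumed falls and onset dates. The conclusion needs only two things: that outside causes changed clinic activity during the after periods, which the protocol expects, and that no described analysis removes that change.

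This is a weakness in what the activity result can support. It does not show that the cohort was rejected or that the risk was hidden.

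**What to change.** 1. State that the activity analysis is a controlled before-after or interrupted time series analysis. Compare patients by offer status (offered, including those who decline, versus not yet offered), or use the staggered site starts, with site and calendar-month effects.
2. Analyze appointments per registered patient-month, and DNAs as a proportion of booked appointments.
3. Confine the Limitations sentence on control groups to patient-completed measures, so that it agrees with Services Outcomes.
4. If dated extracts are not available, report the before-after result as descriptive only. Do not use it to answer question 8 or feed the economic model.

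**Cost.** No further patient contact is needed. The work is a change of wording plus dated activity extracts, for example monthly, and a record of when CHOICE was offered or the site opened. The article says data collection is complete, so whether sites can supply such extracts has to be confirmed.

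**Downside.** The estimate rests on parallel trends, which the months before CHOICE can check only in part. Clinicians may also offer CHOICE selectively, so comparison by offer status reduces selection without removing it.
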